## 2. Methodology

### 2.1. Design of the Intervention Study

This non-randomised, single-group, pre-post-intervention, exploratory trial will evaluate the impact of IST on sarcopenia and dynapenia in adults over 70 years of age across a 16-week period. A detailed timeline of enrolment, interventions, and assessments is presented in Table 1. Each participant will act as their own control, comparing their baseline and post-intervention status. A concurrent comparison group will not be included in this phase, which will focus on feasibility and preliminary effects (see Section 4 for a discussion of limitations). Allocation to different intervention groups is not applicable. The study aims to measure the effectiveness of IST in improving muscle mass, strength and quality of life, as well as its practical applicability. Participants will be recruited in Vitoria (Alava) and Zamudio (Bizkaia, Spain) through Baigene S.L., the Judizmendi Civic Centre (Vitoria-Gasteiz City Council) and the Estadio Vital Fundazioa Foundation.

**Table 1 healthcare-13-01573-t001:** Timeline for Study Participation.

Study Phase	Main Activities	Approximate Timing
Recruitment	Identification of potential participants, initial contact through the collaborating organisations (BAIGENE S.L., Judizmendi Civic Centre, Fundación Estadio Vital Fundazioa).	Prior to the start of the study
	1st Meeting (Information and Consent): Detailed explanation of the study, objectives, exercises; signing of the informed consent form.	Approx. 2–3 weeks before baseline assessment
	2nd Meeting (Criteria Evaluation): Questionnaire (sociodemographic, habits, pathologies, medication); Comprehensive Geriatric Assessment (CGA); Review of analytical data; Anthropometric measurements and Body Composition (height, weight, BMI, InBody for SMM/ASMM); Diagnostic tests for sarcopenia (gait speed, grip strength, and confirmation of low muscle mass with ASMM/ASMI) according to EWGSOP criteria.	Approx. 1–2 weeks before baseline assessment
Baseline Assessment	(Pre-Intervention Assessment): Measurement of physiological variables (BP, HR, SpO2), functional capacity (MVIC of 8 muscle groups, static posture), quality of life (EQ-5D-5L), saliva sampling for genetic analysis.	Week 0 (one week before the start of the IST)
Intervention	IST Programme: 2 sessions/week, 30 min/session, supervised. Progression according to Table 2	Weeks 1 to 16

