The determination of the specific angle for each exercise and participant will be individualised. This will be monitored by the qualified personal trainer or principal investigator, guided by the following principles to ensure effectiveness, safety and comfort:Assessment of Active and Comfortable Range of Motion (ROM): The participant’s active and pain-free ROM for the main joint will be assessed at the beginning of the exercise, avoiding extreme ranges that generate discomfort, pain or instability, considering their ‘specific motor restrictions’.Selection of the Intermediate Angle within the Safe Range: An intermediate angle within the comfortable ROM will be selected that seeks to avoid joint locking or excessive passive tension, and allows the participant to generate a stable and effective Maximal Voluntary Isometric Contraction (MVIC). Although the peak torque angle will not be exhaustively sought, the practitioner will guide the participant to a position in the middle zone of their safe ROM where they subjectively report that they feel comfortable exerting force, favouring optimal actin and myosin overlap.Prioritisation of Safety and Tolerability: If in doubt, the angle that warrants the greatest perceived safety and comfort will be prioritised, even if it is not the theoretically ’optimal’ angle for maximal force production.Recording and Consistency: The individualised intermediate angle, once determined and accurately measured (HALO© digital goniometer), will be recorded and used consistently across all training sessions and MVIC assessments, ensuring standardised stimulus presentation. The aim of this process is to select a joint angle that represents a significant muscular challenge and allows for high fibre activation, within a zone that is biomechanically safe, personalised and well tolerated by each older adult.

The exercises to be performed are: peck deck, pull over, lateral shoulder raise, leg extension, leg curl, lumbar, hip abduction and hip adduction. A visual demonstration of these exercises is shown in Figure 1. The detailed standards for their application (positioning, main muscles, individualised determination of angles, instructions for the three contraction phases and monitoring points) are presented in Table 3.

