#### 2.2.1. Study Outcome Variables (Outcomes)

The following variables will be assessed at pre- and post-intervention (week 0 and week 17, unless otherwise stated) to determine the efficacy and applicability of the IST, as distinguished from the eligibility measures (Section 2.1.1):A.Primary Outcome Variables (Assessment of reversal of dynapenia and sarcopenia):
1.Change in MVIC Knee Extensors:○Specific measurement variable: MVIC of the knee extensors, measured in Newtons (N) with the CIEX SYSTEM machine.○Analysis metric: Absolute change (MVIC_week17_–MVIC_week0_)○Method of aggregation: Mean and Standard Deviation (SD) of the change. The percentage change will also be calculated.○Time point(s): Baseline (week 0) and post-intervention (week 17) assessments.○Clinical Relevance: Knee extensor strength is key to functionality and independence in older adults; its improvement indicates reversal of dynapenia.2.Change at ASMMI:○Specific measurement variable: ASMMI (ASMM in kg/height^2^ in m^2^), measured by bioimpedance (InBody 230).○Analysis metric: Absolute change (ASMMI_week17_–ASMMI_week0_)○Method of aggregation: Mean and SD of change.○Time point(s): Baseline (week 0) and post-intervention (week 17) assessments.○Clinical Relevance: Fundamental diagnostic criterion for sarcopenia (EWGSOP2); an increase indicates improvement in the amount of muscle, essential for metabolic health and reduced frailty.
B.Secondary Outcome Variables

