#### 2.2.2. Pre-Intervention Assessment

One week before starting the 16-week IST, a comprehensive baseline assessment will be performed on the selected subjects to collect baseline data. This assessment, conducted by a physical activity professional and the research group doctor, will allow for detailed monitoring and accurate assessment of the effects of the programme, including the following variables:Physiological Variables: BP and heart rate HR (Omron M3 Comfort^®^ blood pressure monitor, HEM-7134-E, Omron Healthcare Co., Kyoto, Japan) and O2 saturation (OXYM4000 pulse oximeter, Quirumed S.L.U., Valencia, Spain) will be measured. Three resting measurements will be taken per participant, using the mean as the final data.Functional Capacity:○MVIC: The MVIC of each muscle group of the IST programme will be assessed at individualised intermediate angles (determined according to anatomical structure and motor restrictions, recorded with a HALO© digital goniometer). The CIEX SYSTEM machine (Ciex Systems©, Durango, Spain) with sensors and Chronojump software (Chronojump Boscosystems^®^, Barcelona, Spain) will be used for instantaneous measurement and visualisation of strength, tools also used in all IST sessions and for monitoring purposes.○Static Posture Assessment: Participants will be photographed in anatomical position (frontal and sagittal planes) with a Casio Exilim Pro EX-F1 camera (configuration: level tripod, lens at umbilical height, at 4 m, optical zoom, aperture priority, focal length 50 mm, f5.6, ISO 200) [81]. An analysis of documented validity and reliability for postural analysis will be performed with Kinovea^®^ software (v.0.9.x+) [82,83]. Adhesive markers or direct image identification may be used for key anatomical points [84] (sagittal: tragus, C7, acromion, greater trochanter, lateral femoral epicondyle, peroneal malleolus; frontal: acromions, anterior superior iliac spine (ASIS), posterior superior iliac spine (PSIS), patellar centre, tibial malleoli). Postural parameters will be calculated from these points (sagittal: head-neck alignment (HNA) [82], shoulder alignment, estimated spinal curvatures, pelvic tilt [84], knee alignment; frontal: head tilt/symmetry, shoulder height, pelvic symmetry [81], lower limb alignment [82]). Angles (degrees) and distances (cm/mm, after calibration if size reference is used) shall be recorded. Pre-post change will be an outcome of interest. Image analysis shall be performed, if possible, by a blinded assessor (see Section 2.1.3) [83].HRQoL: The EuroQol EQ-5D-5L questionnaire (5 items, 5 dimensions, 5 response levels) will be used [85,86]. This instrument includes two parts: a descriptive system comprising five dimensions (mobility, self-care, usual activities, pain/discomfort, anxiety/depression), each with five response levels, and a VAS where participants rate their overall health.Applicability of the IST Protocol (scales administered post-intervention):○Safety (H1): Assessed by: (1) Analysis of Adverse Events (AEs) (incidence, type, severity, relationship to IST) over 16 weeks (procedures detailed in Section 2.4.3); ‘low risk’ if the incidence of IST injuries is minimal. (2) Perceived Safety: 5-point Likert scale (1 = extremely unsafe, 5 = extremely safe) post-programme, with face validity and based on similar approaches [87]; a mean score ≥ 4 will be expected.○Acceptability (H2): Assessed by compliance rates (≥90% sessions) and overall satisfaction (5-point Likert scale: 1 = extremely dissatisfied, 5 = extremely satisfied) post-programme, using validated measures [88]; a mean satisfaction score ≥ 4 will be expected.○Difficulty (H3): Assessed with a 5-point Likert scale on perceived challenge (1 = not challenging at all, 5 = extremely challenging) post-programme, validated approach [89]; a mean score ≤ 2 will be expected.Genetic Analysis: Saliva samples will be collected using buccal swabs (4N6FLOQSwab, Life Technologies, Waltham, MA, USA). DNA will be extracted from these samples (QIAmp DNA Mini kit, Qiagen, Venlo, The Netherlands) and subsequently quantified (Qubit, Life Technologies). Genetic polymorphisms, specifically Single Nucleotide Polymorphisms (SNPs) and Insertions/Deletions (INDELs), will be analysed in genes associated with the response to strength training, hypertrophy, and strength gains [63,64,65,66,67,68,69,71,72,73]. Specifically, genes linked to the following will be analysed:○Muscle fibre typology: such as ACTN3 (R variant associated with a higher proportion of type II fibres, crucial for strength/power and affected by sarcopenia/dynapenia in ageing) [63,64].○Response to training: including ACE [63,65,66], NRF2, CKMM, MCT1, AMPD1, and the co-activators PPARGC1A and PPARGC1B (involved in mitochondrial biogenesis and exercise adaptation).○Muscle fibre damage and regeneration: genes such as IGF2, MLCK, CASP [72], MMP3 [72], TNC and GDF5 [73], which influence the response to exercise microtrauma and its repair. Moderate exercise-induced muscle damage (EIMD), potentially triggered by IST at long angles, is considered to contribute to remodelling and adaptation.○Vascularisation: NOS3 and VEGFA [67,69], essential for oxygen/nutrient supply, muscle growth and recovery, optimising metabolic stress and hypertrophic response.○Inflammation: TNF-α, CRP [60], IL-6 [60] and IL6-R, which are relevant because inflammation contributes to sarcopenia and modulates the anabolic response [70].○Oxidative damage response capacity: SOD2 [71], CAT and GPX, crucial for muscle recovery and adaptation to training stress.○Fat and carbohydrate metabolism (nutrigenomic factors): Polymorphisms in FABP2, ADRB2, ADRB3, FAT/CD36, UCP2, GCKR, ADCY5 and GIPR, which may influence nutrient uptake and hypertrophic response [74,75,76].

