## 4. Limitations and Strengths of the Study

The results will depend on the comparison between initial and final assessments, and it is crucial that the subjects maintain similar physical and psychological conditions. Working with a vulnerable population may limit the collection of completely objective data despite their actual evolution.

A significant methodological limitation is the absence of a parallel control group. The current single-arm design was chosen for this initial phase to assess the feasibility and preliminary effects of the IST protocol before proceeding to a larger-scale Randomised Controlled Trial (RCT). This feature compromises internal validity, making it difficult to attribute changes to the IST alone with any degree of certainty; factors such as natural progression of the condition, Hawthorne effects or uncontrolled variables may play a role. The inclusion of a control group, preferably through an RCT, as a strategy for future research would strengthen the ability to establish a direct causal relationship and improve internal validity.

Another limitation that may affect internal validity is the exhaustive control and quantification of lifestyle variables (diet, spontaneous physical activity) and medication changes unrelated to the intervention. Although general data are collected (in comprehensive geriatric assessment and for genetic analysis) and participants are instructed to maintain their habits (Section 2.1.3), the absence of detailed baseline assessment and continuous monitoring of these factors limits the ability to completely rule out their role as confounders. In order to partially mitigate this, an analysis of covariance (ANCOVA) could be employed to adjust the results for certain variables, provided they are reliably measured and significant changes are recorded. Future studies would benefit from more rigorous experimental control or more detailed measurement of these confounders.

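### The change in knee-extensor MVIC, a primary outcome, includes a practice gain of unknown size, because there is one listed pre-training test and 32 training sessions follow on the test device with no control arm

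*Protocol article*

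**What the plan says.** Section 2.2.1 defines the first primary outcome as "MVIC of the knee extensors, measured in Newtons (N) with the CIEX SYSTEM machine", analysed as the absolute change, with time points given as "Baseline (week 0) and post-intervention (week 17) assessments". It reads an improvement as reversal of dynapenia.

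Section 2.2.2 describes a single baseline: "One week before starting the 16-week IST, a comprehensive baseline assessment will be performed on the selected subjects to collect baseline data". In Table 1 (Section 2.1), MVIC first appears in the week-0 row, as "functional capacity (MVIC of 8 muscle groups, static posture". The second meeting, one to two weeks earlier, lists gait speed, grip strength and bioimpedance but no MVIC.

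Test and training share their equipment. The machine and software "will be used for instantaneous measurement and visualisation of strength, tools also used in all IST sessions and for monitoring purposes". Section 2.1.2 adds that each participant's individual joint angle "will be recorded and used consistently across all training sessions and MVIC assessments, ensuring standardised stimulus presentation". Leg extension is one of the eight trained exercises, and each contraction ends in a 100% maximal-effort phase. Table 1 gives the exposure: "IST Programme: 2 sessions/week, 30 min/session, supervised", for weeks 1 to 16.

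There is no comparison group (Section 2.1), and the planned test is a paired t-test or its non-parametric analogue (Section 2.3.2). Section 4 concedes that attribution to the training is weakened because "factors such as natural progression of the condition, Hawthorne effects or uncontrolled variables may play a role". Learning of the test is not mentioned.

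**The concern.** A maximal isometric test on an unfamiliar device with live force feedback has a skill component: bracing, pacing the effort and using the display. Here the outcome test and the training share the machine, the display, the joint angle and the instruction to push maximally. Between the two tests each participant repeats that task many times. Any improvement in doing the test adds to the change score, and nothing in the design or analysis separates it from strength.

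The direction is predictable and favours the intervention. The trial is powered on this outcome and is meant to inform a later randomised trial, so an inflated gain would carry into that trial's planning. Strength improvement is also the response in the genetic regressions (H4), where individual differences in learning would be treated as differences in training response.

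**Working it through.** **1. The plan's own figure.** Section 2.3.1 states N = 15 for a paired t-test with d = 0.80, 80% power and two-sided α = 0.05, then 18 after 15% losses. Exact noncentral-t power is 79.0% at n = 14 and 82.1% at n = 15, so N = 15 reproduces. 15 / 0.85 = 17.6, rounded up to 18. The sample-size arithmetic is not in dispute.

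**2. Exposure between the two tests.** 2 sessions × 16 weeks = 32 sessions. At the 90% attendance threshold, 0.90 × 32 = 28.8, so at least 29. Each session has one leg-extension contraction ending in maximal effort.

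**3. SD of the change, from the pilot in Section 2.3.1.** SD = mean change / paired d.
- Left: (296.55 − 224.78) / 1.22 = 71.77 / 1.22 = 58.8 N.
- Right: (306.24 − 263.53) / 0.51 = 42.71 / 0.51 = 83.7 N.

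**4. Sensitivity.** The documents give no practice effect. *Assumption:* practice alone adds 5% or 10% of the pilot baseline, and the true strength gain is zero. Spurious d = practice gain / SD of change. The chance of p < 0.05 is the two-sided noncentral-t rejection probability with n − 1 degrees of freedom and noncentrality d√n.

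| Leg | Practice | Gain (N) | Share of pilot gain | Spurious d | n = 15 | n = 18 |
|---|---|---|---|---|---|---|
| Left | 5% of 224.78 | 11.2 | 16% | 0.19 | 10.6% | 11.9% |
| Left | 10% | 22.5 | 31% | 0.38 | 28.1% | 33.4% |
| Right | 5% of 263.53 | 13.2 | 31% | 0.16 | 8.8% | 9.7% |
| Right | 10% | 26.4 | 62% | 0.31 | 20.6% | 24.3% |

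The nominal level is 5%. A wider assumed range gives 6.3-7.0% (n = 15) and 6.7-7.5% (n = 18) at 3% practice, and 39.9-54.2% (n = 15) and 47.2-63.0% (n = 18) at 15%. The result depends strongly on a quantity that the trial, as planned, will not measure.

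**5. Limits of these inputs.** The pilot differed in population, duration and feedback, so its SDs are only a guide. It used the same type of machine, so its gains may themselves contain some practice.

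**The case against.** **The article may condense the test procedure.** Table 1 gives main activities, not a declared complete list, and warm-up or practice attempts may be in a fuller document. This stands as far as the number of trials is concerned, and no fault is found with that silence. The point rests on the stated schedule: one pre-training occasion, then training on the test device. Several attempts within one visit would reduce the practice component but would not remove it.

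**Participants may not be new to the machine.** Novelty is inferred. Recruitment runs partly through the organisation that ran the pilot on this machine, and the document neither states nor excludes earlier exposure. Earlier exposure would shrink the effect.

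**Section 4 already concedes weak attribution.** It does, its list is illustrative, and the study is called exploratory. But practice on the training device is specific and foreseeable, and it can be reduced without a control arm. A general caveat does not reduce it.

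**Training efforts are not rehearsals of the test.** The maximal phase follows two submaximal phases without rest, and the Discussion expects fatigue to modulate the force exerted. It also names neural activation as an intended mechanism. Both points stand: 32 sessions are not 32 MVIC tests, and a gain without hypertrophy is not thereby an artefact.

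**Other outcomes act as cross-checks.** ASMMI, gait speed and handgrip are not measured on the training machine. They help interpretation but do not correct the MVIC change. Handgrip is weak here because low grip is an entry criterion, so it can rise by regression to the mean. Section 2.1.1 sets entry cut-offs for gait speed and ASMMI too, so the same caution applies to them.

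A reader might go further and infer that a significant result would reflect learning alone. The documents do not support that. It would need a true gain of zero after 16 weeks of maximal-effort training, and the zero-gain figures above are a sensitivity bound, not a forecast.

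**Conclusion.** The point holds as a structural, upward bias in a primary outcome: the MVIC change will contain practice alongside any real strength gain, and the plan neither reduces nor names it. The direction is clear; the size is unknown. Under the stated assumption (5-10% practice, zero true gain, pilot SDs) the false-positive chance is about 9-28% at the 15 participants the calculation requires and 10-33% if all 18 are analysed. The sample-size calculation itself is sound. This should be changed before training starts, because an untrained baseline cannot be recovered afterwards.

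**What to change.** At the existing week-0 visit, once eligibility is confirmed, have each participant complete a full practice knee-extensor MVIC with the display. After rest, repeat the test and use this later result as the baseline. The second meeting is not a suitable place for the practice test, because eligibility and contraindications are still being assessed there.

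Report the mean change between the two pre-training tests, with its confidence interval, beside the 16-week change. Describe it as a lower bound on practice gain. One retest captures early learning only, and fatigue could lower it further, so it does not estimate all learning over 32 sessions.

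State in Section 4 that MVIC change on the training device includes task learning. Interpret it beside ASMMI and gait speed, with handgrip only a partial check, and acknowledge the entry cut-offs on all three. Since Section 2.1.2 scales the submaximal targets to the pre-intervention MVIC, say which of the two tests that refers to.

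The cost is a few minutes of existing staff and machine time, a slightly longer week-0 visit, some possible fatigue between tests and probably a smaller reported gain. A change to how a main outcome is measured may need an amendment under Section 8.1.

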1.Other Indicators of Sarcopenia and Dynapenia:○Handgrip Strength: Specific measurement variable: Maximal handgrip strength, measured in kilograms (kg) (Jamar Dynamometer). Analysis metric: Absolute change from baseline to week 17. Method of aggregation: Mean and SD. Time point(s): Baseline (week 0) and post-intervention (week 17). Clinical Relevance: A component of the sarcopenia diagnosis and a predictor of functionality and mortality.○Gait Speed: Specific measurement variable: Usual gait speed over a 4 m course, measured in meters/second (m/s) (Newtest Powertimer). Analysis metric: Absolute change from baseline to week 17. Method of aggregation: Mean and SD. Time point(s): Baseline (week 0) and post-intervention (week 17). Clinical Relevance: A measure of physical performance, a component of the sarcopenia diagnosis, and a predictor of adverse outcomes.○MVIC of other muscle groups: Specific measurement variable: MVIC for the peck deck, pull over, lateral shoulder elevation, leg curl, low back, hip abduction and hip adduction, measured in Newtons (N) (CIEX SYSTEM). Analysis metric: Absolute change from baseline to week 17. Method of aggregation: Mean and SD of the change per exercise. Time point(s): Baseline (week 0) and post-intervention (week 17). Clinical Relevance: Assesses the training response across different body regions.○Sarcopenia Status: Specific measurement variable: Diagnostic status of sarcopenia according to EWGSOP2 criteria (based on muscle strength, muscle mass, and physical performance). Analysis metric: Change in the proportion of participants meeting the diagnostic criteria from baseline to week 17. Method of aggregation: Frequencies and percentages. Time point(s): Baseline (week 0) and post-intervention (week 17). Clinical Relevance: Quantifies the overall impact of the intervention on the diagnostic status of the condition.2.Health-Related Quality of Life (HRQoL):○Specific measurement variable: The index score derived from the EQ-5D-5L descriptive system and the Visual Analogue Scale (VAS) score of the same questionnaire. Analysis metric: absolute change from baseline to week 17 for both the index score and the VAS score. Method of aggregation: Mean and SD of the changes. Time point(s): Baseline (week 0) and post-intervention (week 17). Clinical Relevance: Measures the overall self-perceived health and the impact of the intervention on multiple dimensions of participant well-being.3.Applicability of the IST Protocol:○Perceived Safety: Specific measurement variable: Score on a 5-point Likert scale for perceived safety. Analysis metric: Mean score post-intervention. Method of aggregation: Mean and SD. Time point(s): Post-intervention (week 17). Relevance: Assesses the participant’s subjective perception of safety, providing data to test hypothesis H1.○Acceptance/Satisfaction: Specific measurement variable: (1) Adherence rate (% of completed sessions); (2) Score on a 5-point Likert scale for overall satisfaction. Analysis metric: Percentage for adherence; Mean score post-intervention for satisfaction. Method of aggregation: Percentage for adherence; Mean and SD for satisfaction score. Time point(s): Adherence monitored continuously during the intervention (weeks 1–16); Satisfaction assessed post-intervention (week 17). Relevance: Measures the feasibility and appeal of the intervention to participants, providing data to test hypothesis H2.○Perceived Difficulty: Specific measurement variable: Score on a 5-point Likert scale for perceived difficulty. Analysis metric: Mean score post-intervention. Method of aggregation: Mean and SD. Time point(s): Post-intervention (week 17). Relevance: Evaluates the perception of technical simplicity, providing data to test hypothesis H3.○Adverse events: Specific measurement variable: Incidence, type, severity and causality (relationship to IST). Analysis metric: Frequencies and descriptive summary. Method of aggregation: Counts and percentages. Time point(s): Monitored continuously during the intervention period (weeks 1–16). Relevance: Assesses the objective safety profile of the protocol, providing data to test hypothesis H1.

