#### 2.3.1. Sample Size Calculation

The sample size was determined after an internal pilot study (N = 50) conducted by the research team (Baigene), using a similar training protocol (CIEX SYSTEM machine) but without visual strength feedback. It was carried out in a population aged ≥65 years with and without sarcopenia/dynapenia and had a duration of 10 weeks. The primary variable for calculation was quadriceps MVIC (N). Pilot results (mean ± SD, Pre vs. Post):Left quadriceps: 224.78 ± 64.49 N vs. 296.55 ± 89.38 N; Cohen’s d (paired samples) = 1.22.Right quadriceps: 263.53 ± 84.66 N vs. 306.24 ± 106.74 N; Cohen’s d (paired samples) = 0.51. Effect sizes were calculated with the mean and SD of the pre-post differences. Given the expected greater improvement with feedback in this protocol, the more specific population (≥70 years with sarcopenia/dynapenia) and the longer duration of the current intervention, a (conservative) d = 0.80 was adopted for the calculation. With G*Power v3.1.9.7, for a related samples *t*-test, detecting d = 0.80 with 80% power and α = 0.05 (bilateral) requires N = 15. Adjusting for 15% losses, 18 participants will be recruited, an adequate number for this pilot exploratory study.

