#### 2.3.2. Analysis Strategy

Primary and secondary quantitative variables will be compared pre-post with Student’s *t*-tests for related samples, after testing for normality (Shapiro-Wilk). If the data are not normally distributed or contain outliers, non-parametric tests (e.g., the Wilcoxon signed-rank test) will be employed. Effect sizes (Cohen’s d) and confidence intervals will be calculated. Multivariate analyses will include a multiple linear regression to explore the influence of genetic and environmental variables on strength and muscle mass improvement, with Bonferroni correction for genetic analyses. Qualitative variables (e.g., sarcopenia diagnosis) will be analysed by using McNemar tests. Applicability variables (Likert scales, adverse events) will be analysed with descriptive statistics and *t*-tests or Wilcoxon tests for pre-post comparisons on Likert scales. Additionally, exploratory subgroup analyses will be performed to assess whether the response to IST on primary variables differs according to sex, age ranges (70–79 vs. ≥80 years) and baseline severity of sarcopenia/dynapenia. Adjustment for baseline covariates will be considered in regression models. The software will be IBM SPSS v29.0 and R v4.3.1.

For the assessment of the secondary hypotheses concerning the applicability (Section 2.2.2) of the IST protocol, specific analyses will be carried out:

Hypothesis H1 (low injury risk): This will be assessed through two approaches. First, Adverse Events (AEs) will be recorded (including their type, severity, and causality), and ‘low risk’ will be inferred if the incidence of IST-related injuries is minimal and comparable to or lower than rates reported in the literature for strength training in older adults [1,33,34,35]. Second, Perceived Safety will be measured post-intervention using a 5-point Likert scale; the approach for this subjective scale is based on similar methods used in previous research [87]. The hypothesis will be supported by a mean score of ≥4.

Hypothesis H2 (high acceptance): This will be assessed by: (1) compliance rate, with a success threshold of ≥90% of completed sessions, and (2) a satisfaction score from a 5-point Likert scale administered post-intervention, using a validated measurement approach [88]. The hypothesis will be supported by a mean satisfaction score of ≥4.

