Hypothesis H3 (low perceived difficulty): This will be assessed using a 5-point Likert scale for perceived technical difficulty post-intervention, based on validated methods [89]. The hypothesis will be supported by a mean score of ≤2.

Hypothesis H4 (Genetic influence). The association between polymorphisms (muscle typology [63,64], inflammation [70,71], tissue regeneration [72,73], energy metabolism [74,75,76]) and improvements in mass/strength (IST) will be analysed by multiple linear regression, adjusting for covariates and with the Bonferroni correction test.

For the Likert-based outcomes (H1–H3), the magnitude of change will also be assessed by calculating Cohen’s d.

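### The rating criteria for H1–H3 turn a bare mean of 15–18 single-item scores into a supported hypothesis, with no allowance for sampling error

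*Protocol article*

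**What the plan says.** Section 2.2.1 makes perceived safety, satisfaction and perceived difficulty secondary outcomes. Each is one 5-point item scored at week 17 (for safety: "Analysis metric: Mean score post-intervention", summarised as mean and SD), and the section says that these items supply data to test H1, H2 and H3.

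Section 2.2.2 gives the figures as expectations, for safety in the words "with face validity and based on similar approaches [87]; a mean score ≥ 4 will be expected". Section 2.3.2 makes them decisions:

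- H1, perceived safety: "The hypothesis will be supported by a mean score of ≥4".
- H2, satisfaction: "The hypothesis will be supported by a mean satisfaction score of ≥4".
- H3, difficulty: "The hypothesis will be supported by a mean score of ≤2".

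H1 and H2 each have a second element. For H1 it is an adverse-event condition, stated thus: "will be inferred if the incidence of IST-related injuries is minimal and comparable to or lower than rates reported in the literature". No number is given. For H2, it is completion of at least 90% of sessions. The section does not say how the two elements combine, and each sentence declaring support names only the mean. H3 has no second element.

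Section 2.3.2 also promises confidence intervals in general terms and descriptive statistics for the Likert scales. The tests it names for those scales are before–after t-tests or Wilcoxon tests.

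**The concern.** A mean from 15–18 people is imprecise on a scale that spans four points. A rule that looks only at whether the observed mean reaches 4 (or 2) will sometimes declare support when the population mean misses the trial's own criterion. Nothing else in the plan supplies the missing allowance for error. The general promise of confidence intervals is not linked to the rule. The named before–after tests cannot be run, because sections 2.2.1, 2.2.2 and 2.2.3 all place these scales after the programme only.

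A mean of an ordinal item can also reach the target while a sizeable minority gives the worst rating. The rule does not react to that, and it is most awkward for a safety item.

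At stake is what the trial may say. It could report isometric training as seen to be safe, acceptable and simple when its data do not exclude a mean on the wrong side of the threshold. Section 5 links confirmed efficacy and applicability to use in geriatric rehabilitation, primary care and community programmes.

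**Working it through.** **1. Number of raters.** Section 2.3.1 states d = 0.80, "80% power and α = 0.05 (bilateral) requires N = 15", and "Adjusting for 15% losses, 18 participants will be recruited". An exact noncentral-t calculation for a two-sided paired t-test gives N = 15 with power 0.821, and 15 / 0.85 = 17.6, rounded up to 18. The figures reproduce. They were derived for quadriceps strength, not for the ratings. About 15–18 people will therefore rate the programme.

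**2. Precision of a mean rating.** The document gives no SD for the ratings, so 0.7, 1.0 and 1.2 are assumed. SE = SD / √n, and the 95% half-width is t(0.975, n−1) × SE.

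| SD | n | SE | 95% half-width |
|---|---|---|---|
| 0.7 | 15 | 0.181 | 0.39 |
| 0.7 | 18 | 0.165 | 0.35 |
| 1.0 | 15 | 0.258 | 0.55 |
| 1.0 | 18 | 0.236 | 0.50 |
| 1.2 | 15 | 0.310 | 0.66 |
| 1.2 | 18 | 0.283 | 0.60 |

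**3. Chance of declaring support when the criterion is missed.** By normal approximation, P(observed mean ≥ 4) = 1 − Φ((4 − μ) / SE). For a true mean μ = 3.8:

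- SD 0.7, n = 18: z = 0.2 / 0.165 = 1.21, probability 11%. With n = 15, 13%.
- SD 1.0: n = 15, z = 0.2 / 0.258 = 0.77, 22%; n = 18, 20%.
- SD 1.2: n = 15, z = 0.2 / 0.310 = 0.65, 26%; n = 18, 24%.

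Ratings are whole numbers and a mean of exactly 4 counts as support, so the true probabilities are a little higher. Replacing 4 by 4 − 0.5/n gives 26% (n = 15) and 23% (n = 18) at SD 1.0. Simulated 5-point ratings with SD about 1.0 gave 27% and 24%. Exact calculation for two rating distributions with SD 0.73 and 0.93 gave 16–25%. The range of about 11–27% is thus not inflated; with the tie correction at SD 1.2 and n = 15 it would be about 30%.

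Further from the threshold the problem shrinks: 12–15% at a true mean of 3.7 and 2–4% at 3.5 (SD about 1.0). H3 is the mirror image: a true mean of 2.2 against the limit of 2 behaves like 3.8 against 4.

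**4. What the mean lets through.** This step needs no assumption about the SD.

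- n = 18, four ratings of 1 and fourteen of 5: (4 × 1 + 14 × 5) / 18 = 74 / 18 = 4.11. Passes with 22% at the worst rating. SD 1.71; 95% CI 3.26 to 4.96.
- n = 15, three ratings of 1 and twelve of 5: (3 + 60) / 15 = 4.20. Passes with 20% at the worst rating.
- n = 18, six ratings of 2 and twelve of 5: (12 + 60) / 18 = 4.00. Passes with one third unfavourable.
- H3, n = 18, four ratings of 5 and fourteen of 1: (20 + 14) / 18 = 1.89. Passes.

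**5. Would a compulsory confidence limit be better?** Requiring the one-sided 95% lower t-limit to reach 4 cuts support at a true mean of 3.8 to about 1–2% (SD about 1.0). It also cuts support at a true mean of 4.2 from 87–88% to 28–31%, and at 4.3 from about 95–97% to roughly 46–55%, depending on the assumed distribution. It can also behave oddly. If all 18 rate 4, the limit is 4.00 and the rule passes. If sixteen rate 4 and two rate 5, the mean is 4.11, SD 0.32, and the limit is 4.11 − 1.74 × 0.32 / √18 = 3.98, which fails although nobody scored lower.

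**The case against.** The trial is single-arm and exploratory, these are secondary applicability outcomes, and preset point-estimate targets are common in feasibility work. A true mean of 3.8 against 4.0 is a small miss. This stands: it lowers the severity and argues against confirmatory machinery. It does not justify the word *supported*; an exploratory aim calls for estimates with intervals.

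Three stronger readings are tempting, and the document does not bear them out.

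- *All three hypotheses are decided by the mean alone.* Only H3 is. H1 also has the adverse-event element and H2 the session-completion element. The figures above describe the rating element of H1 and H2, and their full verdict only if the mean alone decides, which the text leaves open.
- *Support is a coin toss.* At a true mean of exactly 4 the chance is 55–58%, but any point-estimate criterion is met about half the time when the truth sits on the cut-off, at any sample size. The relevant figures are those below the threshold.
- *An unhappy minority would stay hidden.* It is hidden from the rule, not from the report. Mean, SD and descriptive statistics are planned, and an SD of 1.71 would be conspicuous. Adverse events are recorded separately by type, severity and causality.

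It is also fair to say that section 2.2.2 alone voices only an expectation. The difficulty arises from section 2.3.2.

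**Conclusion.** The point holds in a limited form. Section 2.3.2 declares the rating element of H1 and H2, and the whole of H3, supported on a bare sample mean from 15–18 people, with no interval attached and no test that can be applied. Under an assumed SD of 0.7–1.2, a true mean 0.2 on the wrong side of the threshold is called supported in about 11–27% of trials. By arithmetic alone, 4 of 18 or 3 of 15 participants can choose the worst safety rating and the rule is still met. The probabilities depend on assumed SDs and rating distributions; the counts do not.

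Severity is minor to moderate. The sample-size calculation is not in question, and the case for a compulsory confidence-limit gate is not made.

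**What to change.** In section 2.3.2, with matching words in 2.2.2:

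- Describe the figures of 4 and 2 as descriptive feasibility targets.
- Report each mean with its 95% CI and the number and proportion at each rating. Name the counts at 1–2 for safety and satisfaction, and at 4–5 for difficulty.
- When the mean reaches the figure but the CI includes values on the wrong side, write that the target was met on the point estimate, not that the hypothesis is supported.
- Remove the before–after tests for these scales, since there is no baseline rating.

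Do not make clearing a confidence limit a condition for meeting the target. The interval should govern the strength of the wording only.

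The cost is a few sentences in two sections and no new data. The downside is a more modest claim: with SD 0.7–1.2, an observed mean of about 4.35–4.66 (4 plus the half-width) would be needed before the 95% CI lay wholly on the favourable side of 4.
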